#### Intervention Description

The development of this intervention and the decisions made during that process, including the recent changes that were informed by the single-site pilot study, are described in detail in a prior paper [32]. Therefore, we have prepared a structured table (see Table 1) outlining the sequential steps in the intervention and refer readers to our prior paper for additional detail.

**Table 1 table1:** Intervention components.

Intervention stage	Steps	Other notes
Introduction to study (prior to study start date)	Digital video (.mp4) describing the intervention (~5 minutes in length) is distributed to the pharmacy manager. Pharmacy manager disseminates the video. All staff members view the video. Lead pharmacists are asked to include the video in the orientation package for new pharmacists and pharmacy technicians and those who may have missed the initial meeting.	Each pharmacy has a regular, site-specific “all hands” meeting each month. In the pilot and feasibility study, this meeting was identified as the appropriate venue to disseminate intervention information.
Early implementation (prior to study start date)	Confirm with the managing pharmacist that all intervention pharmacies have viewed the video at the “all hands” staff meeting. Deliver a set of 30 doses of naloxone (presently, individually packaged Narcan nasal spray) to each pharmacy in numerically marked bags imprinted with “Not for Sale.” Deliver a set of 500 consecutively numbered harm reduction referral slips to each pharmacy (customized for each pharmacy location). Deliver sets of reminder post-it notes to pharmacies. Deliver the requested number of yard signs to each pharmacy (based on the number of routes of travel around the pharmacy). Ensure that pharmacy’s in-store television has access to the scrolling reminder text.	Digital copies of all of the visual materials described here (3, 4, and 5) are freely available in a prior publication [32].
Launch (on the study start date)	Reminder post-its placed in visible areas on the interior of the dispensing location (eg, staff side rather than patient side). Harm reduction referral cards placed at each checkout for easy access. Yard signs placed outside the building in visible locations where traffic (vehicle or foot) is common. Scrolling television banner will be enabled to run continuously through the intervention. “76.7% of overdoses happen at home. Bystanders who witness an overdose can be effective in reducing overdose mortality. Ask us about how you can save a life with naloxone today!”	Digital copies of all materials for this project are provided as attachments to the single-site pilot study manuscript [32]. All marketing materials will be standardized, except that the referral and recovery resource information (referral cards) will be specific to each local community.
Implementation (continuous after start)	There are 4 primary procedural events that result in offers of naloxone as well as provision of harm reduction cards. Three are initiated on the pharmacy side and were tailored for this project based on harm reduction management plan recommendations for clinicians from the Centers for Disease Control and Prevention [43]. Those are: 1. Prescription fill for a medication for opioid use disorder; 2. High-dose opioid prescription (50 morphine milligram equivalents or greater); 3. Request for syringes without a prescription, even if syringes are not available at the site. The fourth is initiated on the patient side: 4. Patient request for naloxone. The existence of these guidelines is specifically not intended to preclude offers or dispensing in other situations (eg, pharmacist discretion).	Naloxone will be dispensed based on the patient’s ability to pay, as determined by the pharmacist or pharmacy technician. Referral cards will be provided at each procedural event regardless of whether naloxone is dispensed. Pharmacy staff may either briefly acknowledge the card (“We wanted to share with you some community resources that may interest you”) or not. The cards can be placed inside the prescription bag (they are one-quarter of a standard 8.5 × 11 in page) or handed directly to the patient.
Ongoing supplies (continuous after start)	The pharmacy manager, as well as the lead pharmacist at each site, will be instructed to contact the research team a minimum of 3 business days prior to any intervention component (eg, naloxone, referral cards, and reminder post-its) being exhausted. The research team will then provide additional supplies.	Based on the single-site pilot, the initial materials provided at launch are expected to be sufficient for the project duration.
Fidelity monitoring (~1 month after start)	Approximately 1 month after the intervention’s launch, we will conduct a single fidelity site visit to each intervention site. This will include inspection for presence of all materials (eg, yard signs, television messaging, and field observations). Any major concerns will be addressed with the pharmacy manager.	Since our orientation to this project is pragmatic, we do not plan to engage in extensive fidelity monitoring, as this would not be available in a real-world implementation of the program [44].

An essential component of the PharmNet intervention is that pharmacies have naloxone on hand that they can dispense at no cost to patients who cannot afford it. Such dispensing accounted for roughly two-thirds of the overall increase in dispensing in our single-site pilot [32]. However, we had identified that the independent pharmacies in this project did not have direct access to free or reduced cost naloxone and often must order it in response to prescriptions. Thus, as part of the intervention, the study team developed memoranda of understanding (MOUs) with (1) one of the largest nonprofit agencies that provides free naloxone to the state of Indiana, (2) a secondary nonprofit as a “backup,” and (3) the pharmacy organization. These MOUs were initially designed to serve for the duration of the project and facilitated the structured transfer of naloxone at the needed volume to participating pharmacies at no cost. The MOUs did not reference a specific limit on available doses but indicated the possibility that the nonprofit may, at times, not have free naloxone available to distribute—leading to our engagement of the “backup” organization. Importantly, now that procedures and agreements are in place, the study team will be able to “withdraw” from the MOUs at the end of the study and facilitate similar MOUs directly between the nonprofits and pharmacy organization to continue the supply of naloxone without an intermediary. Facilitating this supply of naloxone to the pharmacy was perceived as critical to the program’s success in the single-site pilot [32] and may be important to supporting the sustainability of ongoing programs of this kind.

### Sampling Plan: Sample Size Determination and Power Analysis

As noted above, we will conduct this study among 7 independent community pharmacies, with a 4:3 allocation to intervention and control arms. With 80% power (α=.05, 2-tailed), this sample will allow us to detect large effect sizes (Cohen *d*=2.68). In our single-site pilot study, we observed a large increase in the average number of monthly naloxone doses dispensed (from 9.67 doses/month prior to the intervention to 19 doses/month during the intervention). We further do not expect that the control pharmacies will substantially vary in the number of naloxone doses dispensed over time.

We made the decision to conduct this smaller, pilot randomized controlled trial, because although our single-site pilot study produced a sizeable effect on naloxone dispensing, we could not be certain that it was not attributable in part to unmeasured confounding (eg, external trends in naloxone dispensing). In addition, recruiting and providing materials (especially naloxone) to a large sample of pharmacies represents a substantial cost, and so, prior to investing in a more conservative, fully powered, and pragmatic study, we wanted to obtain additional data. Thus, we plan to report all *P* values exactly rather than by threshold and undertake a nuanced interpretation of the findings [45], including a visual inspection and presentation of the trends in intervention and control pharmacies, with the purpose of determining whether a large, randomized study appears to be an appropriate and valuable investment.

Since the pharmacy manager has agreed in principle to participation among all 7 individual pharmacies, we do not intend to apply any inclusion or exclusion criteria but note that individual-level data collection will still be subject to exclusion via declining to participate at the point of informed consent.

### Analysis Plan

#### Primary Outcomes

The number of naloxone doses dispensed will be treated as the overall number of doses, which is the sum of those that are (1) sold, as tracked by the pharmacy’s record system; and (2) dispensed free of cost, as tracked by sequentially numbered doses stored separately in the pharmacy. This value will be obtained retrospectively for the 3 months prior to the intervention and then monthly for 3 months (the duration of the intervention).

#### Secondary Outcomes

As noted previously, this study will collect, describe, and in some cases analyze secondary outcomes to facilitate the interpretation of the study findings. These data and analyses will be treated as exploratory.

We will produce a count of the referral cards distributed by each intervention pharmacy by manual inspection of the individually numbered cards provided to each pharmacy. In addition, using a pretest-posttest methodology, we will collect individual-level data from pharmacy staff members (pharmacists and pharmacy technicians). Measures collected prior to the intervention will include the following (see Multimedia Appendix 1 for a copy of each instrument):

Sociodemographic information (age, gender, race, ethnicity, and sexual identity);Information about current pharmacy practice experience;Comfort with multiple harm reduction practices, as used in our prior study to explore harm reduction latent classes [27]; andMeasures of stigmatizing beliefs about people who use drugs, which combine components of the 2019 Brief Opioid Stigma Scale by Yang et al [46] and work by author [name]’s interdisciplinary group of medication for opioid use disorder patients and providers, which is in review.

The postintervention survey will include the comfort and stigma items (above) as well as additional sets of items (see Multimedia Appendices 2-3):

Intervention acceptability (4 questions adapted from the Consolidated Framework for Implementation Research [33]);A set of questions targeted at implementation optimization validated by Livet et al [47]; andFour evaluative items developed by our team to potentially inform future work (eg, “If you could wave a magic wand, how would you improve the PharmNet intervention?”).

#### Statistical Analyses

We will analyze the primary outcome using a generalized linear mixed model with a Poisson distribution to compare change over time of the number of naloxone doses dispensed between study arms. We will include fixed effects for group, time, and their interaction and a random effect for pharmacy ID to account for repeated measures within pharmacy.

We do not anticipate any missingness in the primary outcome because the data are objective measures and can be accessed retrospectively if needed. If missing data are present in the individual-level data (>5%), we will perform multiple imputation by chained equations to assess the degree to which missingness affects the results. If missing data meaningfully affect the findings, we will report the analyses with imputation. If individuals provide a survey at one time point but not another (eg, a pretest without a posttest or vice versa), we will analyze the data as unmatched in our mixed models.

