**Methods:**

We will conduct a 3-month randomized controlled pilot trial consisting of 2 parallel groups with a 4:3 allocation ratio. A group of 7 independent pharmacies from rural areas in Indiana will be randomly assigned to either the PharmNet intervention arm (n=4) or the control arm (n=3). The primary outcome will be overall naloxone dispensing (both at cost and free), and secondary outcomes will include the distribution of referral cards and multiple variables at the level of individual staff members. Dispensing data will be collected for the 3 months prior to the intervention and the 3 months of the intervention, and all other data will be collected using a pretest-posttest design. The primary analysis will be a generalized linear mixed model with a Poisson distribution with fixed effects for group, time, and their interaction and a random effect for pharmacy ID to account for repeated measures within pharmacies.

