### Design

#### Trial Design

The PharmNet pilot trial will be a cluster randomized trial consisting of 2 parallel groups and a 4:3 allocation ratio of intervention to control. The independent pharmacy organization participating in the project consists of 8 pharmacies, of which 1 was the pilot and feasibility test site [32]. The remaining 7 pharmacies will be allocated using a web-based random sequence generator (conducted by author [name]), such that 4 pharmacies will be selected to implement PharmNet, and 3 pharmacies will serve as controls (pharmacy practice as normal). The workflow for the study is provided in Figure 1**.**

This study will utilize partial blinding; the research team and the pharmacy manager (who supervises all 7 pharmacies, see description in our prior paper [32]) will not be blinded to assignment because it would not be possible to do so, but individual pharmacists, pharmacy technicians, and others working in the control arms will not be aware that their pharmacies are serving as controls.

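### The primary Poisson model's test of change by arm does not use the 7 randomised pharmacies as its replicates, so its P value is too small if pharmacies differ in their true change

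*Protocol article*

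**What the plan says.** The unit of randomisation is the pharmacy. As the Trial Design section puts it, "The PharmNet pilot trial will be a cluster randomized trial consisting of 2 parallel groups and a 4:3 allocation ratio of intervention to control", and "4 pharmacies will be selected to implement PharmNet, and 3 pharmacies will serve as controls".

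The outcome is a count of naloxone doses. Under Primary Outcomes, "This value will be obtained retrospectively for the 3 months prior to the intervention and then monthly for 3 months (the duration of the intervention".

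The Abstract (Methods) states that "The primary analysis will be a generalized linear mixed model with a Poisson distribution". The Statistical Analyses section says the model compares change over time between arms and contains "fixed effects for group, time, and their interaction and a random effect for pharmacy ID to account for repeated measures within pharmacy". These sentences fix the distribution, the fixed effects and one random effect. No pharmacy-by-time random effect is named.

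The Sampling Plan section states "With 80% power (α=.05, 2-tailed), this sample will allow us to detect large effect sizes", given there as Cohen d = 2.68. It cites the single-site pilot's rise "from 9.67 doses/month prior to the intervention to 19 doses/month during the intervention" and adds, without a figure, that control pharmacies are not expected to vary much over time.

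**The concern.** Hypothesis 1 is a statement about change, so its test is the group-by-time term. A pharmacy intercept appears in both the pre and the post period and drops out of the difference. What is left to judge the effect against is Poisson noise in the dose totals. That noise shrinks as stores get busier, even though the number of randomised units stays at 7.

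Two things would then go unmeasured by the error term: pharmacies whose dispensing drifts by different amounts for local reasons, and monthly counts that vary more than a Poisson variable. Either makes the P value too small and the confidence interval too narrow. The stake is the reported result for Hypothesis 1 and the first of the two routes to a larger trial under Next Steps, which asks for a strong, significant effect.

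**Working it through.** **1. The plan's own figure.** Inputs from the Sampling Plan section: 4 v 3 pharmacies, two-sided α = 0.05, 80% power. A two-sample t test by the noncentral t distribution, with 4 + 3 − 2 = 5 df, gives a detectable d of 2.684, and power 0.799 at d = 2.68. A normal approximation gives (1.960 + 0.842) × √(1/4 + 1/3) = 2.14, so it does not reproduce the figure. The power statement therefore takes the 7 pharmacies as replicates, on 5 df.

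**2. Standard error of the planned test.** With only an intercept at pharmacy level, the variance of the interaction (log scale, pre/post coding) is approximately the sum of 1/(total doses) over the four arm-by-period cells. At 9.67 doses/month for 3 months:
- intervention arm: 4 × 3 × 9.67 = 116 doses per period
- control arm: 3 × 3 × 9.67 = 87 doses per period
- variance = 2/116 + 2/87 = 0.0402, SE = 0.20

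**3. Actual variance if pharmacies differ in true change.** Let τ be the SD between pharmacies of the true log change. The variance becomes 0.0402 + τ²(1/4 + 1/3). The real type I error of a nominal 5% test is about 2 × [1 − Φ(1.96 × √(0.0402 / actual variance))]. τ is not in the documents, so the values below are assumptions. For scale, τ = 0.2 means a typical store drifting by about 20%, or 2 doses on 9.67.

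| τ (assumed) | Actual variance | Type I error, formula | Type I error, full model fitted to simulated trials |
|---|---|---|---|
| 0 | 0.0402 | 5.0% | 4.4% |
| 0.1 | 0.0460 | 6.7% | 7.1% |
| 0.2 | 0.0635 | 11.9% | 13.1% |
| 0.3 | 0.0927 | 19.7% | 21.1% |
| 0.4 | 0.1335 | 28.2% | 31.8% |

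The simulations assume no intervention effect and an SD of 0.5 for log pharmacy level. They run slightly above the formula because the larger stores dominate the pooled change. Rounded across the simulation runs, the figures are about 5%, 7%, 13%, 22% and 31%.

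**4. Sensitivity to other unstated inputs.**
- Volume: at 5 doses/month the variance in step 2 is 2/60 + 2/45 = 0.0778, and the inflation is smaller, about 9% to 21% for τ from 0.2 to 0.4.
- Coding of time: with a linear monthly trend, 5.8% at τ = 0, 11% at 0.2 and 18% at 0.3.
- Overdispersion alone (τ = 0, 9.67 doses/month): about 12% at a monthly variance/mean ratio of 1.5 and 19% at 2.0.

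**5. Pharmacy-level comparison.** A t test on the 7 values of log((post+0.5)/(pre+0.5)) had type I error between 4.6% and 5.0% in the settings of step 3.

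**6. Power at the pilot effect.** The ratio is 19/9.67 = 1.96. At τ = 0, power is about 95% for the planned test and about 80% for the pharmacy-level test (78% with the level SD of 0.5 used here). At τ = 0.3, the figures are about 85% and 44%.

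**The case against.** The strongest reply is that the inflation is not demonstrated. If all 7 pharmacies share one true change and counts are exactly Poisson, the planned test is correct at about 5%. The documents lean weakly that way: one organisation, one manager over all sites, mostly rural stores, and controls expected to be stable. This stands as a limit on size. A reader might infer that the false-positive rate is 12% to 30%, but that range needs an SD of change of roughly 0.2 to 0.4, or comparable overdispersion, and the protocol gives neither. A single-site pilot cannot estimate the former.

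Second, this is a condensed article, and an unseen analysis plan may cover overdispersion, degrees of freedom or robust errors. A reader might infer that the plan has decided against them; silence does not support that. Nor does the text literally say intercept only. What it does fix is a Poisson distribution and one pharmacy effect, justified by repeated measures, and that structure does not carry variation in change.

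Third, this is a pilot. The Sampling Plan section promises exact P values rather than thresholds, nuanced interpretation and visual inspection, and Next Steps allows the larger trial without significance. A reader might infer that a false positive leads straight to the larger trial. The documents do not make significance the only gate. That lowers the severity, but the P value and interval for Hypothesis 1 will still be reported, and reporting P exactly does not help if its error term is too small.

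**Conclusion.** The point holds in conditional form. On the natural reading, the primary test of change by arm draws its error from dose counts and not from the 7 randomised pharmacies, whereas the protocol's own detectable effect is computed on those pharmacies with 5 df. The P value is too small and the interval too narrow whenever pharmacies differ in true change or counts are overdispersed. At the pilot's volume the type I error runs from about 5% (no such variation) to about 31% (log-change SD 0.4), and it is lower at lower volumes. These figures rest on assumed SDs and pre/post coding of time. Given the pilot purpose and the second go-ahead route, this is a should-fix. The planned model cannot absorb the variation if it exists, and the pharmacy-level test holds its level either way.

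**What to change.** Before analysis, base the test of Hypothesis 1 on one 3-month pre total and one 3-month post total per pharmacy. Compare log((post+0.5)/(pre+0.5)) between arms with a t test and confidence interval on 5 df; the added 0.5 keeps the ratio defined if a total is zero. Support it with the exact randomisation test over the C(7,3) = 35 possible allocations. Its smallest P is 1/35 = 0.029 and the next is 2/35 = 0.057, so only the single most extreme allocation falls below 0.05.

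Keep the mixed model as a sensitivity analysis, with a random pharmacy-by-period effect and small-sample degrees of freedom. Negative binomial variance alone is not a remedy, because months rather than pharmacies would still be the replicates.

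The change is to analysis wording only and needs no new data. The cost is nominal power at the pilot effect: from about 95% to about 80% with no variation in change, and from about 85% to about 44% with an SD of 0.3. In the second case, part of the mixed model's apparent power comes from an error term that is too small.

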#### Data Management and Monitoring

As noted earlier in this paper, individual-level data from pharmacy staff members will be collected in QualtricsXM, which is a secure platform. Only the research team will have access to the raw data in QualtricsXM. Any identifying information used to match pretest and posttest data will be removed prior to the distribution of the data set for analysis. Based on the opinion of a professional biostatistician, additional data may be redacted prior to public data set release in the specific case that it might allow the identification of an individual staff member.

#### Harms

We do not anticipate that any harms would be accrued to participating pharmacies as a result of participating in this study. Based on our single-site pilot study, we strongly suspect that the burden on staff members will be minimal (since this is a pragmatic study, that is by design). However, pharmacies will always have the option to withdraw from the trial. In the unlikely event that such a thing occurs, we will report the data as they exist and describe the impetus behind the withdrawal in our final write-up. Similarly, we do not anticipate any risks to individual pharmacy staff participants related to completing study questionnaires, which are voluntary. However, we will follow all appropriate IRB procedures in the event of a loss of confidentiality.

